#### Estimation methods

The primary outcome variables in most of our statistical models will be continuous and will therefore typically be estimated using the Ordinary Least Squares method. As secondary outcomes, we will also examine dichotomous outcomes—such as stunting or wasting—as dependent variables, in which case we will use both linear probability models and Probit models to implement the regression analysis. Homoscedasticity in the residuals will be tested and if rejected, the SEs will be adjusted for heteroscedasticity following.^38^ All statistical analyses will be conducted using Stata, V.17 or higher.

### Ethics and dissemination

The study protocol is approved by the Institutional Review Board of the Ethiopian Public Health Institute (protocol no: EPHI-IRB-481–2022), Michigan State University (protocol no: STUDY00007996) and International Food Policy Research Institute (protocol no: DSGD-23–0102). Written informed consent will be obtained from each respondent and participants will be informed that they may withdraw from the study at any time. Confidentiality of all collected data will be given high priority during each stage of data handling. Individual names and personal information of respondents will be kept confidential and data sets will be kept anonymous for analysis. Patient consent for publication is not required.

The study’s findings will be disseminated through several communications channels, including stakeholder workshops, various local and international conferences and technical reports. Additionally, the findings will be shared through research articles and submitted for publication in peer-reviewed journals.

## Discussion

The results of this study will inform researchers and policymakers on the impact of AFM_1_ in milk on children’s nutrition outcomes and will have implications for the transforming dairy value chains in Ethiopia. Ethiopia has recently adopted strict AFM_1_ standards in milk and other dairy products, which has led to dairy farmers dumping their milk instead of selling it in the market.^12^ An earlier study showed that cancer risk from AFM_1_ consumption was expected to be extremely low.^12^ However, if AFM_1_ has other harmful health effects, such as compromising child growth, then the strict regulations could be justified. In this study, we can determine whether AFM_1_ levels are higher when animals are fed particular feedstuffs, which—if AFM_1_ is correlated with poorer child growth outcomes—will help identify which crops should not be included in dairy feed. But if our work finds that AFM_1_, independently of livestock feed, causes poor child growth outcomes, then the focus need not just be on reducing AFB1 in dairy feed, but also on technologies that can remove AFM_1_ from milk before it is given to children or further processed for other dairy products.

Our work will contribute to rational policymaking and risk communication at local and national levels on whether AFM_1_ poses a risk to children’s health. It will help policymakers and risk communicators in crafting messages balancing the benefits, risks and health outcomes associated with dairy consumption. Secondarily, there could be economic benefits to dairy producers if AFM_1_ is found to have minimal (or no) adverse child growth outcomes, so that standards and regulations can be set at levels appropriate to the true risk, and so that dairy products do not need to be discarded because of overly stringent regulations.^4 39^

There are some limitations of our study. Since a randomised control trial in this context is not feasible, we use a quasi-experimental approach to understand the risks and benefits of child milk consumption in this context and aim to minimise the risk of bias by controlling for observable confounding factors. We use the 24-hour dietary recall and the limitation of this method is that it only captures food intake in the 24 hours prior to the interview. To address this, we will collect data on the consumption of food groups in the past 7 days and also ask whether the milk quantity consumed in the last 24 hours reflects the typical quantity consumed by the child.

Despite these limitations, the results of our study will inform policy decisions on the appropriate AFM_1_ standards for commercial milk and dairy products, on measures to mitigate AFM_1_ risks and on improvement of knowledge of AFM_1_ risks among dairy consumers, producers, and other dairy value chain actors.

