**Ethics and dissemination:**

The protocol is approved by the Institutional Review Boards of the Ethiopian Public Health Institute (EPHI-IRB-481–2022), Michigan State University (STUDY00007996) and International Food Policy Research Institute (DSGD-23–0102). Written informed consent will be obtained from all participants, who may withdraw from the study at any time. Confidentiality of collected data will be given high priority during each stage of data handling. The study’s findings will be disseminated through stakeholder workshops, local and international conferences, journal articles and technical reports.

Strengths and limitations of this studyThis is the first study that assesses how aflatoxin M_1_ (AFM_1_) in milk affects child growth in Ethiopia, controlling for socioeconomic, nutritional and environmental factors.This research compares the health risks of AFM_1_ with the benefits of milk consumption for children.The findings will be used to inform feasible, health risk-based policies on AFM_1_ in milk, not just in Ethiopia, but potentially in other nations worldwide.The findings of this study would not allow for causal inference or finding a toxicological mechanism because of the observational design, but would aid in the understanding of the relationship between AFM_1_ exposure and child growth.

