### Sample size calculations

Using the 2016 Ethiopia Demographic Health Survey^22^ and focusing on our primary anthropometric outcome variable, we have mean height-for-age z-scores (HAZ) in children under the age of 36 months of −1.46 (SD=1.56). With the significance level set at 5%, power at 80%, allowing for 10% attrition between survey rounds, and accounting for that not all children consume milk, the study requires approximately 1000 children to detect a 0.3 SD improvement in child HAZ. This minimum detectable effect size corresponds to the estimated association between household cow ownership and child HAZ (children starting at 6–18 months of age) in a study by Hoddinott *et al* in rural Ethiopia.^23^ Since we focus directly on children’s dairy consumption rather than cattle ownership, and our exposure variable is continuous rather than dichotomous, the expected magnitude of the association is likely to be larger than the association documented in Hoddinott *et al*.^23^ Thus, we expect this sample size to offer sufficient precision to detect positive and/or negative associations between AFM1 exposure and growth outcomes in this population.

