### Sampling procedures

Our formative research found that feed ingredients and type varied by herd size and season. Based on these findings, we will classify the dairy cow-owning households into small herd size (one to three cattle) and large herd size (four or more cattle) and randomly select a total of 500 households each from both groups. The two study districts have a list of herd sizes to provide the sampling frame. Within these two groups, all households have an equal chance of being selected.

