### Explanatory variables

Child’s milk consumption and AFM_1_ levels in milk are the key explanatory variables in this study. Child’s milk consumption will be measured through a 1-day quantitative multiple-pass 24-hour recall interview, consisting of four steps designed to enhance respondent’s recall accuracy.^24^ We will ensure that all days of the week are proportionately represented during the dietary recall, to account for day-of-the-week effects on food intake. We will also collect a second, non-consecutive day 24 hours recall (repeat), within 2–10 days of the first recall, from a randomly selected subsample of children to account for the day-to-day variability of dietary intake within individuals and for nutrients estimation.

At the baseline and the end-line visits, we will collect milk samples (2000 samples in two rounds). AFM_1_ testing in milk, analysis of dilution of milk, nutrients composition and pathogens testing (including *Escherichia coli and Campylobacter* spp) will be conducted at Ethiopian Public Health Institute (EPHI) laboratory following standard operating practices for handling, processing and storing samples.

AFM_1_ in milk samples will be detected by using a commercial ELISA kit (catering to catalogue no. 961AFLM01C-ULTRA), manufactured by Helica Biosystems of Santa Ana, California, USA.^25^ The methodology for conducting the test will be based on the manufacturer’s guidelines. Standards and samples of 200 µl will be replicated in precoated plates. The resulting mixture will be incubated for 2 hours, followed by washing and the addition of conjugates. After the completion of 15 min of additional incubation and subsequent washing, enzyme substrate of 100 µl will be added to each well, permitted to incubate for 15 min and afterwards stopped using 100 µl of stop reaction. Finally, optical density measurements will be taken at 450 nm for each microwell using a microplate reader. Calculation of AFM1 levels achieved by means of a logarithmic standard curve will require an R^2^ value of no less than 95%. The average results from duplicate readings will be used for the presentation of results.^25^

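### The Discussion's readings of the AFM1 coefficient, as causing poor growth or as minimal, are not supported by the observational design, zero-null tests and uncorrected spot AFM1 samples

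*Protocol article*

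**What the plan says.** All references are to the protocol article.

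- **Use of a reassuring result.** The Discussion expects economic benefit to producers if AFM1 "is found to have minimal (or no) adverse child growth outcomes, so that standards and regulations can be set" in line with the true risk. Policy recommendations on AFM1 are also one of the four listed objectives.
- **Use of an adverse result.** The Discussion considers what should follow if the work finds that AFM1 *causes* poor growth. Among the limitations it states: "we use a quasi-experimental approach to understand the risks and benefits of child milk consumption".
- **The disclaimer.** The strengths and limitations statement after the abstract says: "The findings of this study would not allow for causal inference or finding a toxicological mechanism because of the observational design".
- **The analysis.** Under Data analysis, equation (2) adds an AFM1 exposure term (coefficient β_A) to a least squares model with milk intake, milk nutrients, pathogens, maize and other covariates. The stated inference is a test of whether contaminated milk is associated with lower HAZ, and a joint test that the milk and AFM1 coefficients are both zero.
- **The exposure.** Under Explanatory variables: "we will collect milk samples (2000 samples in two rounds", one at baseline and one at end line. Under Study design these visits are 18 months apart. Sampling procedures reports from the formative work that "feed ingredients and type varied by herd size and season".
- **The contrast with milk intake.** Intake gets a repeat recall in a subsample, six-monthly phone calls used to adjust for consumption variability, and a stated limitation. AFM1 concentration gets none of these.

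**The concern.** How β_A is read decides what the study tells regulators, and the article leaves both directions open to misreading.

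If β_A is clearly negative, the Discussion's wording invites a causal claim that the same article says the design cannot carry.

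If β_A is near zero, nothing in the article separates a small effect from an effect that could not be seen. A test against zero cannot establish that an effect is minimal. The joint test is less suited still, since it can reject on the benefit of milk alone. A spot milk sample is also an imperfect measure of a child's usual exposure over 18 months when the cow's feed changes with the season. Error of that kind commonly shrinks a regression coefficient. A falsely reassuring conclusion about a contaminant in young children's food would be the costly mistake.

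**Working it through.** **1. The plan's own sample size.** Sample size calculations says: "the study requires approximately 1000 children to detect a 0.3 SD improvement in child HAZ". It uses 5% significance, 80% power, SD 1.56, 10% attrition and an unstated share of milk consumers. Two-sided testing is assumed here.

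- Read as 0.3 SD: n per group = 2(1.96 + 0.84)²/0.3² ≈ 175, so 350 in total and 350/0.9 ≈ 389 after attrition.
- Read as 0.3 HAZ units: n per group = 2(1.96 + 0.84)²(1.56/0.3)² ≈ 425, so 850 in total and 850/0.9 ≈ 945.
- With an unequal split, N = (1.96 + 0.84)²(SD/δ)²/[p(1 − p)]/0.9. An assumed consumer share p of 0.89 gives 990 on the first reading; p of 0.62 gives 1001 on the second.

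Because the share is not stated, 1000 can be neither confirmed nor called wrong. What matters here is the source of the effect: "This minimum detectable effect size corresponds to the estimated association between household cow ownership and child HAZ". No AFM1 effect, exposure spread or reliability enters, so the section's closing statement of sufficient precision for AFM1 has no calculation behind it.

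**2. Power under exposure error (illustration).** From the protocol: SD of HAZ 1.56, 1000 children, 10% attrition. Assumed: 80% of the remaining 900 drink milk, giving n = 720; true effect b = −0.20 HAZ per SD of usual AFM1; reliability λ of one spot sample 0.3 to 0.5; classical error.

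With classical error the coefficient per unit of exposure is multiplied by λ, and the coefficient per observed SD is b√λ. SE = 1.56·√(VIF/n), and power = Φ(|b|√λ/SE − 1.96).

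- n = 720, VIF 1: SE = 1.56/√720 = 0.058. λ = 0.3: 0.110/0.058 = 1.88, power 0.47. λ = 0.5: 0.141/0.058 = 2.43, power 0.68. The effect would be missed in 53% and 32% of such studies.
- n = 720, VIF 2: SE = 0.082; power 0.27 and 0.41.
- n = 558 (62% of 900), VIF 1: SE = 0.066; power 0.38 and 0.57.

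The VIF 2 line is rough. If the error is independent of the covariates, they can explain at most a share λ of the observed exposure, so VIF cannot exceed 1/(1 − λ), which is 1.43 at λ = 0.3 and 2 at λ = 0.5.

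**3. What a zero estimate would exclude.** With n = 720, the 95% half-width per observed SD is 1.96 × 0.058 = 0.114 HAZ (VIF 1) or 0.161 (VIF 2). Dividing by √λ puts it per SD of usual exposure, treating λ as known:

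| λ | VIF 1 | VIF 2 |
|---|---|---|
| 1.0 | 0.114 | 0.161 |
| 0.5 | 0.161 | 0.228 |
| 0.3 | 0.208 | 0.294 |

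At λ = 0.5 and VIF 1 a zero estimate does exclude a loss of 0.20; at λ = 0.3 it does not. The reading turns on a reliability that the article does not plan to estimate.

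**4. What the second round can give.** With exchangeable replicates, the mean of two samples has reliability 2λ/(1 + λ): 0.46 for λ = 0.3 and 0.67 for λ = 0.5.

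**5. The causal wording.** The disclaimer and the Discussion's *causes* cannot both stand. Estimation methods lists only ordinary least squares, linear probability and probit models. No instrument, discontinuity or similar device is described that would make the approach quasi-experimental, and the Introduction calls the study a prospective longitudinal cohort.

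**The case against.** A reader might infer that the article lays down a policy rule under which a non-significant β_A means low risk. It does not. The sentence is a conditional remark about possible benefits to producers, and no standard is tied to a p-value. Another sentence in the Discussion speaks correctly of AFM1 being correlated with growth. Nor is it right that non-significance is the only evidence: regression gives β_A an interval, and several secondary growth outcomes are planned.

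A reader might also infer that the plan is shown to be biased toward the null. That needs roughly classical error, which the documents neither state nor rule out. The article does not say whether the exposure term is concentration alone or concentration times intake. In the second case it shares recall error with the milk term. If both terms entered on the log scale and concentration were independent of intake, β_A would still shrink by the reliability of log concentration, because log exposure minus log intake is log concentration; the article fixes neither condition. Residual confounding could also push β_A away from zero.

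The figures depend on assumptions. Consumer share, effect size, reliability and VIF are not in the documents. The SD of 1.56 is a raw survey value, not a residual SD or the SD of change in HAZ.

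Finally, an article may leave calibration details and margins to an analysis plan. That is fair for the technique. It does not remove the conflict over causality, nor the contrast between a correction announced for milk intake and none for AFM1 concentration, whose sampling error is absent from the stated limitations.

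**Conclusion.** The concern holds as a problem of interpretation, not as a numerical error. The contradiction between the causal disclaimer and the Discussion is certain from the text. It is also plain that minimal has no definition, that the stated tests are against zero, and that the sample size was not derived for AFM1.

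Attenuation of β_A is likely but conditional on roughly classical error, and confounding could act in either direction. Under the stated assumptions, power for −0.20 HAZ per SD is 0.47 to 0.68 at reliability 0.3 to 0.5, and lower with fewer consumers or with collinearity. These figures do not show that a null result would be uninformative: at reliability 0.5 without collinearity, a zero estimate would bound the effect at about 0.16 HAZ per SD. They show that the strength of any reassurance cannot be judged without the reliability. The change is worth making because it is cheap and protects the conclusion that the study exists to inform.

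**What to change.** 1. Keep the baseline AFM1 exposure as the main analysis, since only that sample precedes the growth interval. Use the end-line sample as a replicate to estimate the reliability of log AFM1. Report a regression-calibrated β_A beside the naive one, with an interval that carries the uncertainty in the reliability. Show the two-round mean as a sensitivity analysis. State that samples 18 months apart are imperfect replicates, because season and lasting changes in feed both enter the difference between them.
2. Fix in advance the HAZ loss that would matter. Call the effect minimal only if the confidence interval of the corrected β_A excludes that loss; otherwise report the result as inconclusive.
3. Replace *causes* and *quasi-experimental* in the Discussion with associational wording that agrees with the disclaimer, and list AFM1 sampling error as a limitation.

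The cost is a little more analysis on samples already planned, agreement on one margin, and a few words of text. Corrected intervals will be wider, so an inconclusive result becomes more likely.
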